### Stopping rules

In serious diseases (like high-grade locally advanced or metastatic osteosarcoma), the trial may need to stop prematurely if there is evidence of inefficacy [32]. Thus, this two-stage phase II clinical trial with a futility stopping based on Simon minimax criterion will be prematurely stopped if there is fewer than 3 DCS among the first 19 patients treated with mycophenolate mofetil.

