### Study design

This prospective study is an open-label, single-arm, two-stage phase II clinical trial of mycophenolate mofetil orally administered at the dose of 5 g/day (or lower) for 4 cycles (28 days/cycle) or until disease progression or unacceptable toxicity. This two-stage phase II clinical trial plans to involve a total of 27 adolescent and adult patients with high-grade locally advanced or metastatic osteosarcoma. In Stage 1, 19 patients will be enrolled, and the trial will continue to Stage 2 and enroll additional 8 patients only if at least 3 patients in Stage 1 achieve the primary endpoint.

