### Withdrawal criteria

More than 4 weeks of study drug interruption due to toxicity;Disease progression or any significant deterioration in the health of the patient;Unacceptable toxicity;Occurrence of another illness which precludes further participation in this trial;Significant protocol noncompliance;Development of an illness or situation which would affect assessments of clinical status and study endpoints to a significant degree;Pregnancy;Patient lost to follow-up; orWithdrawal of informed consent.

Patients who withdraw or are withdrawn prematurely will be replaced only if they discontinue during the first four weeks due to reasons other than toxicity.

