### Interventions

Mycophenolate mofetil (CellCept®, Roche Laboratories Inc., Nutley, New Jersey) in 500 mg/tablet will be used in this trial. All adult patients (aged ≥18 years) will be treated with mycophenolate mofetil at the initial dose of 5 g/day, twice daily, while adolescent patients (aged 13–17 years) will be treated with mycophenolate mofetil at the initial dose of 3–5 g/day based on the patient’s body surface area (BSA) at enrollment (i.e., 5 g/day for those with a BSA of > 1.5 m^2^, 4 g/day for those with a BSA of 1.26 to 1.5 m^2^, and 3 g/day for those with a BSA of 1.0–1.25 m^2^). Self-administration of the study drug will take place on an outpatient basis (under parents’ supervision in some cases, as appropriate). Patients will return unused tablets at each follow-up visit; the unused tablets will be counted and recorded to determine compliance. One cycle is considered to be 4 weeks, and the next cycle of the treatment with mycophenolate mofetil will start only after safety assessments are done.

Allopurinol at the dose of 300–600 mg/day will be coadministered orally, twice daily, for blockage of the guanine salvage pathway [23]. All adult patients (aged ≥18 years) will be treated with allopurinol at the dose of 600 mg/day twice daily, while adolescent patients (aged 13–17 years) will be treated with allopurinol at the dose of 300 or 600 mg/day twice daily based on the patient’s body weight at enrollment (i.e., 600 mg/day for those with a body weight of ≥40 kg, and 300 mg/day for those with a body weight of < 40 kg). Evidence in kidney transplant recipients suggests that concurrent administration of mycophenolate mofetil with allopurinol is innocuous [24, 25].

Available palliative and supportive care for disease-related symptoms should be offered to all patients. Palliative radiotherapy is allowed for local pain control, provided that (1) the patient does not have progressive disease, (2) no more than 10% of the patient’s bone marrow is irradiated, and (3) the radiation field does not encompass a target lesion. Surgical resection of the disease is permitted after documentation of response. All the patients will be instructed not to take any other medications (including over-the-counter products) during study participation without prior consultation with the investigators.

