### Dose modifications

Each patient will be closely monitored for toxicity, and the dose of mycophenolate mofetil may be adjusted according to individual patient tolerance at the discretion of the investigators (Table 1). The dose of mycophenolate mofetil may be reduced by 1–2 g/day or withheld for some Grade 3 or Grade 4 toxicities, whenever clinically needed (Tables 2). All dose-limiting toxicities will be managed following the standard protocol of a participating study site. The dose of mycophenolate mofetil for cycle 1 to cycle 4 of new patients may be reduced, at the discretion of the investigators, by 1–2 g/day, if more than 33% of the former patients experience a dose-limiting toxicity at that dose level and require dose de-escalation after treatment.

**Table 1 Tab1:** Dose de-escalation schema of mycophenolate mofetil

Dose level	Dose of mycophenolate mofetil in adult patients
0 (initial dose)	5 g/day (5 tablets twice a day)
-1	4 g/day (4 tablets twice a day)
−2	3 g/day (3 tablets twice a day)
−3	2 g/day (2 tablets twice a day)
−4	1 g/day (1 tablet twice a day)

Note that the initial dose (dose level 0) of mycophenolate mofetil in pediatric patients is the dose that is adjusted based on the patients’ BSA at enrollment; dose level –x in pediatric patients will be the initial dose–x g/day

**Table 2 Tab2:** Hematological and non-hematological criteria for suggested dose modification of mycophenolate mofetil

Toxicity^(a)^	Hold study treatment	Dose modification
*Hematological criteria*		
Grade 4 bone marrow hypocellular	No^(b)^	Decrease one dose level^(c)^
Grade 4 febrile neutropenia	No^(b)^	Decrease one dose level^(c)^
Grade 4 neutrophil count decreased	No^(b)^	Decrease one dose level^(c)^
≥ Grade 3 of other hematologic toxicities	No^(b)^	Decrease one dose level^(c)^
Sepsis & any Grade 3 infection	Yes until ≤ Grade 2^(d)^	Resume at one dose level lower^(c)^
Sepsis & any Grade 4 infection	Yes until ≤ Grade 2^(d)^	Resume at two dose level lower^(c)^
*Non-hematological criteria*		
Grade 3, except for: delayed puberty, growth suppression, breast atrophy, erectile dysfunction, diarrhea^(e)^, vomiting^(e)^, and AST/ALT increased or other biochemical laboratory abnormalities without any clinically significant sequelae	No^(b)^	Decrease one dose level^(c)^
Any Grade 4 toxicity	No^(b)^	Decrease two dose level^(c)^

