### Participant recruitment

Potentially eligible patients will be identified by a treating physician, and approached by a study nurse. Accrual is expected to be complete within 2.5 years after trial initiation.

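### Stopping and Stage 2 entry depend on disease control alone, and the one cross-patient toxicity rule permits a dose cut but requires no review or pause

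*Protocol article*

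**What the plan says.** All references are to the protocol article.

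- **Stopping rules:** one criterion, inefficacy. The trial "will be prematurely stopped if there is fewer than 3 DCS among the first 19 patients treated with mycophenolate mofetil".
- **Study design and Sample size determination:** Stage 2 will "enroll additional 8 patients only if at least 3 patients in Stage 1 achieve the primary endpoint". The drug is called promising at 6 or more successes at the end of the study. Neither decision carries a safety condition.
- **Dose modifications:** the one rule that looks across patients. Its trigger is met "if more than 33% of the former patients experience a dose-limiting toxicity at that dose level and require dose de-escalation after treatment". The response to that trigger is optional: the dose "of new patients may be reduced, at the discretion of the investigators". The permitted cut is 1 or 2 g/day.
- **Rationale for the experimental dose:** repeats that the starting dose may be lowered at the investigators' discretion and adds that the protocol would then be amended. Under Ethical approval and trial status, amendments need ethics approval before they take effect.
- **Interventions:** adults start at 5 g/day plus allopurinol. Adolescents start at 3–5 g/day by body surface area. Also, "the next cycle of the treatment with mycophenolate mofetil will start only after safety assessments are done".
- **Background and Data monitoring:** a phase I trial is judged unnecessary, and a data monitoring committee is declined because the trial is small and the investigators can watch each patient closely.

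**The concern.** The safety provisions act on one patient at a time: Table 2 dose changes and their escalation footnotes, withdrawal criteria, infection prophylaxis, and a safety check before each cycle. They protect the patient already on treatment. They do not answer whether the next patient should start at the same dose.

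The 33% clause is the only text that addresses that question, and it says what investigators may do. It sets no count at which they must look and no pause in accrual while they decide. If a change of starting dose is chosen, an amendment and ethics approval must follow, and the text does not say whether accrual at the old dose continues meanwhile. Followed to the letter, the trial could enrol all 19 Stage 1 patients at the starting dose and open Stage 2 without any recorded cross-patient review of DLTs.

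This matters more here than in many single-arm trials of a known drug. The dose rationale claims a satisfactory long-term safety record at 2–3 g/day and describes 4–5 g/day in more guarded terms. Patients may be as young as 13. Safety and tolerability is the stated secondary objective, yet no trial-level decision uses it.

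**Working it through.** **1. The plan's own figures (Sample size determination).** Inputs: n1 = 19, continue if at least 3 DCS; n = 27, promising if at least 6 DCS; p0 = 0.12, p1 = 0.32; α = β = 0.10.

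- P(Stage 2 opens) = 1 − P(X ≤ 2), X ~ Bin(19, p). At 0.12: 1 − (0.088 + 0.228 + 0.280) = 0.403. At 0.32: 0.969.
- P(promising) = Σ over x ≥ 3 of P(X = x) · P(Bin(8, p) ≥ 6 − x). At 0.12: 0.094. At 0.32: 0.900.

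Both error limits hold, and an exhaustive search finds 27 to be the smallest total that meets them. The efficacy design is sound. No toxicity term enters either probability.

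**2. How far the 33% clause depends on an unstated schedule.** The article gives no DLT rate, so all rates here are assumptions. Chance that the clause is met at least once by patient 19, counting one in three as above 33%:

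| Assumed true DLT rate | Checked after every patient | Checked once, at 19 (7 or more) |
|---|---|---|
| 10% | 0.30 | 0.002 |
| 20% | 0.59 | 0.07 |

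The same sentence therefore behaves very differently depending on when someone looks. Even when it is met, no action is compelled.

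**3. The threshold as counts at fixed reviews.** Take reviews at 6, 12, 19 and 23 patients, with the boundary as the smallest x for which x/n exceeds one third: 3/6 = 50%, 5/12 = 42%, 7/19 = 37%, 8/23 = 35%. By this convention exactly one in three does not cross.

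Example for the first review at a 20% rate: P(X ≥ 3 of 6) = 1 − 0.8⁶ − 6(0.2)(0.8⁵) − 15(0.04)(0.8⁴) = 1 − 0.262 − 0.393 − 0.246 = 0.099.

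Later reviews follow by exact recursion: carry forward the distribution of counts below the boundary, add the next group's binomial count, and remove what crosses. Before the review at 23, multiply by P(Stage 2 opens) from step 1, with DLT taken as independent of DCS. Cumulative probability of a pause:

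| True DLT rate (assumed) | by 6 | by 12 | by 19 | by 23, DCS 32% | by 23, DCS 12% |
|---|---|---|---|---|---|
| 10% | 0.02 | 0.02 | 0.02 | 0.02 | 0.02 |
| 20% | 0.10 | 0.13 | 0.15 | 0.17 | 0.16 |
| 33% | 0.31 | 0.44 | 0.56 | 0.62 | 0.58 |
| 40% | 0.46 | 0.63 | 0.77 | 0.83 | 0.79 |
| 50% | 0.66 | 0.84 | 0.94 | 0.97 | 0.95 |

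**4. Practicality.** "Accrual is expected to be complete within 2.5 years after trial initiation". If accrual is even, 2.5 × 365.25 / 27 = 33.8 days per patient, and 28 / 33.8 = 0.83 patients enter during one 28-day cycle. A review needs no routine hold on recruitment.

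**The case against.** The case against is substantial. The drug has been used for decades, the trial is open-label with 27 patients, and the Data monitoring section gives reasons for its choice. Patients withdraw for unacceptable toxicity or for more than four weeks' interruption. Table 2's footnotes count non-recovery after 7 days as a further toxicity and allow treatment to end after more than three reductions. A changed starting dose goes through an amendment and ethics approval. At one patient about every 34 days, with a safety check before each cycle, practice may come close to patient-by-patient review. Patients are replaced only in narrow circumstances (they "will be replaced only if they discontinue during the first four weeks due to reasons other than toxicity"), so severe toxicity may also lower the DCS count and reach the futility rule indirectly. All of this stands, and it lowers the severity. None of it obliges a decision across patients.

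It can also be said that a journal article leaves review schedules to the full protocol. That would cover silence. Here the article has its own sections on stopping, dose modification and monitoring, and it states the rules as futility-only and discretionary.

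Three stronger readings are tempting and not supported:

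- A reader might infer that the investigators would ignore toxicity. The text says they will monitor closely and act in time; it only leaves the cross-patient step unspecified.
- A reader might infer that 33% is an ambiguous threshold, since 2/6 and 4/12 exceed 0.33 but not one third. That arises only when the number reviewed is a multiple of three. Reviews at 7, 13, 19 and 23 give the same boundary (3, 5, 7, 8) on both readings, with a pause probability of 0.207 at a 20% rate.
- A reader might infer that a data monitoring committee is required, or that the rule would save a stated number of DLTs. Neither follows: the existing investigators can do the review, and patients enrolled after a pause also carry risk.

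**Conclusion.** The point holds as a worthwhile, inexpensive safety improvement. Trial-level stopping and the opening of Stage 2 rest on DCS alone, and the one pooled toxicity rule is permissive, with no review points and no accrual pause. Nothing in the Simon calculation is wrong.

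The textual gap does not depend on any assumed rate. The pause probabilities do: they rest on assumed DLT rates, DLT independent of DCS, reviews at 6, 12, 19 and 23, and a starting dose that does not change during the trial. If toxicity lowers the chance of disease control, fewer trials reach the review at 23 and the last step shifts slightly, as the 12% column shows. The figures describe how the proposed rule would behave; they do not measure harm in the trial as planned.

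**What to change.** Turn the 33% clause into a mandatory review by the existing investigators:

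1. Review at fixed counts of patients treated at the starting dose level, for example 6, 12, 19 (with the Stage 1 analysis) and 23. Count by level and not by grams, because "the initial dose (dose level 0) of mycophenolate mofetil in pediatric patients is the dose that is adjusted" for body surface area, so adolescents at level 0 belong in the count.
2. Count every DLT requiring de-escalation at any time on treatment up to the review. A cycle 1 window would miss later infections that the present clause includes.
3. Write the boundary as counts: at least 3/6, 5/12, 7/19 or 8/23.
4. Crossing it pauses accrual at that dose until the review is recorded and reported to the ethics committee. The recorded outcome is to resume, lower the starting dose by amendment, or end the trial.
5. Stage 2 does not open while a pause is unresolved.
6. Keep the discretionary dose cut below the boundary, so that staying under it is no licence to continue.

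Cost: one amendment paragraph and a short table, from adverse-event data already collected. No extra patients, staff or procedures are needed, and the DCS cut-offs stay as they are. The downside is an unnecessary pause in about 2% of trials at a true DLT rate of 10% and 17% at 20%. That is why crossing should pause and not stop: if every crossing ended the trial, power at a 20% DLT rate would fall to about 0.900 × (1 − 0.168) = 0.75.

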### Data management

This trial uses Research Electronic Data Capture (REDCap), a secure web-based application for managing clinical trial databases. The study essential documents will be retained, as the investigators’ responsibility, for a minimum of 15 years after completion or discontinuation of the study or for a longer period if required.

### Data monitoring

In this open-label, single-arm phase II clinical trial, Data Monitoring Committee (DMC) is not needed because of a small number of patients involved (*n* = 27) and that the investigators can closely monitor the safety of all individual patients taking a known drug with a known dose (open-label). This allows the investigators to take appropriate action in time.

### Statistical analysis plan

All patients who receive at least one dose of mycophenolate mofetil will be included in an intention-to-treat analysis. Patients’ baseline demographics will be summarized using descriptive statistics. Study drug administration will be described in terms of the total number of cycles (or days) administered, the median (range) of cycles (or days) administered, dose intensity, and reasons for deviations from planned therapy. Adverse events will be collected after the patient has taken the first dose of mycophenolate mofetil.

The PFS at 16 weeks or DCR (the primary endpoint) will be measured as a binary variable: DCS or DCF. The PFS and OS will be summarized using the Kaplan-Meier method and displayed graphically as appropriate. For patients lost to follow-up, they will be censored at the date of the last follow-up visit. Median PFS and OS (and their corresponding 95% confidence intervals) will also be provided.

All statistical analysis will be executed using IBM SPSS Statistics for Windows, version 22.0, with a *p* value of less than 0.05 considered to indicate statistical significance. It is possible that the decision rule of this single-arm, two-stage phase II clinical trial may need to be adapted from the original plan [33]. If the attained sample size at the end of this study is different from the one that is initially planned due to any reason, a statistical testing will be conducted by calculating the *p* value with the sample size at the stopping stage conditioned on the observed value [34, 35]. The Jennison-Turnbull confidence interval may be used by treating the observed sample size at the stopping stage like the planned sample size [36].

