### Exclusion criteria

History of another malignancy within 5 years prior to study entry, except curatively treated non-melanotic skin cancer or other solid tumors curatively treated with no evidence of disease for > 3 years;Current treatment with another investigational agent and/or systemic anticancer therapy within 4 weeks prior to enrollment;Surgery and/or radiotherapy for curative intent within 1 month prior to enrollment;History of allergic reactions attributed to mycophenolate mofetil, MPA, allopurinol (including the presence of HLA-B*5801, indicating an increased risk of severe cutaneous adverse reactions to allopurinol), ivermectin, trimethoprim-sulfamethoxazole (or sulfa drugs), acyclovir or any ingredients of the drugs;History of severe or uncontrolled medical conditions or laboratory abnormality;Impaired renal function (with creatinine clearance of < 45 mL/min);Known or suspected pregnancy or breastfeeding;Any other conditions in which mycophenolate mofetil, allopurinol, ivermectin, trimethoprim-sulfamethoxazole, or acyclovir is contradicted;Unable to swallow oral medications;Major surgery within 4 weeks prior to study entry; orSignificantly altered mental status.

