### Study procedures

Twelve visits are scheduled for this trial and a summary of study procedures for each visit is presented in Table 3. The expected duration of study participation is about 4–5 months. All patients must agree to use two reliable, effective contraceptive methods simultaneously for at least 7 days prior to the first dose of the study drug and for 6 weeks following the last dose of the study drug, unless absolute sexual abstinence is the chosen method of contraception. This is because mycophenolate mofetil is known to cause a high frequency of miscarriage (~ 50%) and severe birth defect in the unborn baby [26, 27].

**Table 3 Tab3:** Scheduled visits and assessments

Procedures	Study Visits											
	SV	C_1_w_0_	C_1_w_1_	C_1_w_2_	C_1_w_4_	C_2_w_2_	C_2_w_4_	C_3_w_2_	C_3_w_4_	C_4_w_2_	C_4_w_4_	FV
Informed consent obtained	×											
Inclusion/exclusion criteria assessments	×											
History taking	×											
Physical examination	×	×	×	×	×	×	×	×	×	×	×	×
ECOG status	×											
Electrocardiogram	×											
Lab test for complete blood count	×			×	×	×	×	×	×	×	×	×
Lab test for fasting blood glucose	×											
Other lab tests^(a)^	×			×	×		×		×		×	×
Circulating tumor cells		×^(b)^	×^(b)^	×		×		×		×		
Biobank collection	×				×		×		×		×	×
Urine analysis^(c)^	×			×	×		×		×		×	×
Stool examination	×											×
Pharmacokinetic study^(d), (e)^		×	×									
Pain score & Quality of life		×			×		×		×		×	×
Review of concomitant medications	×	×	×	×	×	×	×	×	×	×	×	×
Monitoring for adverse events			×	×	×	×	×	×	×	×	×	×
Tumor assessment^(f)^	×						×				×	

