SV = screening visit; C_x_w_y_ = cycle x week y; FV = final visit. ^(a)^ Lab tests include Na, K, Cl, HCO3, Ca, Mg, P, albumin, AST, ALT, ALP, total bilirubin, direct bilirubin, BUN, Cr, PT, PTT, INR, and LDH; ^(b)^ Blood obtained from the pharmacokinetic study will be used for measurement of circulating tumor cells on C_1_W_0_ and C_1_W_1_ so that no additional blood samples will be collected; ^(c)^ Urine analysis includes a urine pregnancy test for a female patient of childbearing age; ^(d)^ Blood samplings (at 0, 0.5, 1, 1.5, 2, 3, 4, 6, 8, 10, and 12 h); ^(e)^ Additional samplings for drug monitoring may be required when drug dosage is modified (after ≥7 days of drug administration with an adjusted dose level); ^(f)^ Tumor assessment by a computerized tomography (CT) scan (of the chest ± other organs, if required) or magnetic resonance imaging (MRI), done at baseline, 8 ± 1 weeks and 16 ± 1 weeks after initiation of study drug administration; in case of objective tumor response (complete response or partial response), confirmatory imaging studies will be performed at least 4 weeks after initial documentation of response

There are three drug regimens to be used for prophylaxis of possible infection during study participation: (1) ivermectin (12 mg/day) for 2 days before Cycle 1, Week 0 [28], (2) trimethoprim-sulfamethoxazole (160/800 mg/day) once daily from Cycle 1, Week 1, until discontinuation of mycophenolate mofetil [29], and (3) acyclovir (400 mg/day) twice daily from Cycle 1, Week 1, until discontinuation of mycophenolate mofetil [30]. No evidence of PK drug-drug interactions between any of these regimens and mycophenolate mofetil is reported [31].

Should mycophenolate mofetil prove beneficial to some patients (i.e., evidence of stable disease or partial response) at the end of the treatment period (on Week 16), the study treatment will be given to those patients in the extension period until one of the withdrawal criteria is met. Additional visits will be scheduled during the extension period (Table 4).

**Table 4 Tab4:** Additional visits and assessments in the extension period

Procedures	Study Visits								
	C_5_w_2_	C_5_w_4_	C_6_w_2_	C_6_w_4_	C_7_w_2_	C_7_w_4_	C_x_w_2_	C_x_w_4_	FV
Physical examination	×	×	×	×	×	×	×	×	×
Lab test for complete blood count	×	×	×	×	×	×	×	×	×
Other lab tests^(a)^		×		×		×		×	×
Circulating tumor cells	×		×		×		×		
Biobank collection		×		×		×		×	×
Urine analysis^(b)^		×		×		×		×	×
PK study^(c)^									

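### Adverse-event collection starts after the first mycophenolate dose, so the protocol-required ivermectin days before it fall outside the collection window

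*Protocol article*

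**What the plan says.** The start of adverse-event collection is stated, in the Statistical analysis plan section: "Adverse events will be collected after the patient has taken the first dose of mycophenolate mofetil". Table 3 (Study procedures) is consistent with it. The row labelled "Monitoring for adverse events" is blank at the screening visit and at C1w0, and is marked at all ten visits from C1w1 to the final visit.

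The Study procedures section introduces the prophylaxis thus: "There are three drug regimens to be used for prophylaxis of possible infection during study participation". The first regimen is "ivermectin (12 mg/day) for 2 days before Cycle 1, Week 0". The second is "trimethoprim-sulfamethoxazole (160/800 mg/day) once daily from Cycle 1, Week 1, until discontinuation of mycophenolate mofetil", and acyclovir follows the same calendar as the second.

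The Exclusion criteria bar patients with a history of allergic reaction to, among others, "ivermectin, trimethoprim-sulfamethoxazole (or sulfa drugs), acyclovir or any ingredients of the drugs". The analysis population is set by "All patients who receive at least one dose of mycophenolate mofetil will be included in an intention-to-treat analysis".

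**The concern.** The protocol places ivermectin within study participation but outside the period in which adverse events are collected. It is the only one of the three prophylactic drugs treated this way, and the article gives no reason. The exclusion of patients with previous ivermectin allergy shows that the authors regard reactions to it as possible.

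Two things are at stake. The first is completeness: the safety record of the regimen as actually given has a gap at its start. The second is attribution. There is no control arm to show how often an event would occur without mycophenolate. Under the Dose modifications section, toxicities guide individual dose reductions, and the share of earlier patients with dose-limiting toxicity can lower the dose for new patients. An event already present before the first mycophenolate dose should be recognisable as such, and the schedule has no adverse-event recording at the point where that could be established.

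**Working it through.** The plan gives no figure to reproduce. The check compares the timing of events stated in different parts of the protocol article.

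| Step | Timing | Source | Adverse events collected? |
|---|---|---|---|
| Ivermectin | 2 days before Cycle 1, Week 0 | Study procedures, prophylaxis paragraph | No |
| C1w0 visit | Week 0; physical examination and concomitant-medication review marked, adverse-event row blank | Table 3 | No mark |
| First mycophenolate dose | Week 0 (inferred, see below) | Visit schedule; pharmacokinetic sampling at C1w0 | Starts after this dose |
| C1w1 visit | Week 1; first adverse-event mark | Table 3 | Yes |
| Trimethoprim-sulfamethoxazole and acyclovir | From Cycle 1, Week 1 | Study procedures, prophylaxis paragraph | Yes |

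The article does not state in so many words that the first mycophenolate dose is taken at C1w0. The visit numbering and the pharmacokinetic sampling from 0 to 12 hours at that visit imply it.

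An ivermectin reaction then has four possible courses:

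1. **It begins and resolves before the first mycophenolate dose.** It lies wholly before the window and is not collected as an adverse event.
2. **It begins before the dose and the patient never takes mycophenolate.** The window never opens for that patient, who is also outside the analysis set, because membership requires a mycophenolate dose.
3. **It begins before the dose and persists afterwards.** It falls inside the window. The first scheduled monitoring is at C1w1, about a week into mycophenolate, and no earlier adverse-event entry is scheduled to show that it was already present.
4. **It begins after the dose.** It is collected in the ordinary way.

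Courses 1 and 2 are outside the stated window. Course 3 is captured, but its attribution is weaker than it need be. Course 4 is not affected.

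**Size.** The exposure outside the window is 2 days per patient, for 27 patients if both stages run and 19 if the trial stops after Stage 1. The documents give no ivermectin reaction rate and no split between the four courses, so an expected number of uncollected events cannot be derived.

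**The case against.** The strongest reply is that the window suits its purpose. The Study objectives section frames the secondary objective around mycophenolate, and ivermectin is prophylaxis, not a treatment under evaluation. Starting collection at the first dose of the investigational drug matches that objective, and the text and Table 3 do not contradict each other. This stands: the gap concerns the safety record of the regimen more than the estimate of mycophenolate toxicity. It does not dispose of course 3, which bears on what is attributed to mycophenolate.

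Three stronger readings are tempting, and the documents do not support them.

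- **That all ivermectin reactions are lost or the exposure is unmonitored.** Reactions that persist past the first dose or begin after it are inside the window. The patient is also examined at C1w0, with a medication review, so a reaction may be noticed even though nothing there has it entered as an adverse event.
- **That such events leave no safety record at all, or are bound to be misattributed.** A condensed article commonly leaves serious-event reporting and the recording of onset and causality to the full protocol and case report form, which are not shown. Only the stated collection window can be criticised.
- **That a probability of unrecorded events can be given.** With an assumed reaction rate q, the chance of at least one reaction among 27 patients is 1 − (1 − q)^27, which gives 0.238 at q = 0.01 and 0.750 at q = 0.05. That is the chance of any reaction, not of an uncollected one. If, again by assumption, half persisted into the window, the rates become 0.005 and 0.025 and the results 0.127 and 0.495. The answer depends on inputs for which the documents give no basis.

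The absence of a data monitoring committee adds little, since it has no specific bearing on whether these 2 days are logged.

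**Conclusion.** The point holds in a limited form. A stated rule, repeated in Table 3, leaves one protocol-required exposure outside adverse-event collection. Reactions confined to the period before mycophenolate, and reactions in patients who never start it, are not collected as adverse events under that rule. Those that carry over into treatment are collected without a scheduled pre-dose record to help separate them from mycophenolate toxicity.

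The consequence is for the safety record of the regimen and for attribution. No reliable rate can be attached to it. The primary endpoint, the two-stage decision rule and the sample size are untouched. The conclusion assumes that ivermectin is given to all patients, as the unconditional wording indicates, that the first mycophenolate dose is at C1w0, and that the full protocol does not widen the window stated in the article. It is a low-cost improvement, not a flaw that threatens the trial's conclusions.

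**What to change.** Make three linked changes:

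1. Reword the sentence in the Statistical analysis plan section so that adverse events are collected from the first dose of any protocol-required drug, which in practice means from ivermectin onward.
2. Add an adverse-event monitoring mark at C1w0 in Table 3, completed before the first mycophenolate dose.
3. List events with onset before the first mycophenolate dose separately, including those in patients who never receive mycophenolate. Leave the main mycophenolate safety table and the analysis set defined as they are now.

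No dose, schedule or clinical rule changes. The cost is one reworded sentence, one mark at a visit that already takes place, a few extra entries and one short listing, some of which will contain events unrelated to mycophenolate. If the full protocol already provides for collection before mycophenolate, it is enough to bring the article's sentence and Table 3 into line with it.
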